#### 2.6.4. Sample Size

As this is a pilot feasibility study, a formal sample size calculation based on statistical power was not performed. Approximately 30 patients per year who meet the eligibility criteria are treated at the Department of Special Care Dentistry of Nagasaki University Hospital. Therefore, a target sample size of 30 participants was considered feasible within the planned study period and sufficient to assess feasibility outcomes, including recruitment, acceptability, data completeness, and safety, to inform the design of future definitive trials.

## 3. Discussion

The aim of this pilot feasibility study is to determine novel and clinically relevant insights relating to the use of a HFNC during routine dental treatment. Dental procedures frequently require prolonged mouth opening with spontaneous nasal breathing. Patient posture can also compromise nasal airflow and hinder saliva swallowing. These factors can contribute to discomfort, anxiety, and stress. Currently, there are limited evidence-based strategies specifically designed to address the common physiological and psychological challenges in dental settings. Importantly, certain dental procedures (e.g., rubber dam isolation) are known to increase discomfort and treatment distress due to swallowing or breathing difficulties [11].

The physiological mechanisms underpinning the potential utility of HFNCs in dental settings warrant careful consideration, particularly because dental procedures impose unique respiratory challenges that differ from those in the perioperative or critical care contexts.

Figure 2 provides a conceptual framework summarizing the proposed physiological mechanisms by which HFNC therapy may influence breathing comfort during dental treatment, particularly under conditions of sustained mouth opening and spontaneous breathing. During routine dental procedures, prolonged mouth opening may lead to nasal airflow limitation, impaired breathing–swallowing coordination, and increased breathing work, which can contribute to physiological stress responses.

These conditions may amplify patient concerns, such as anxiety, choking, or difficulty swallowing saliva, further contributing to dental fear (in both adult and pediatric populations) [10].

By delivering warmed and humidified high-flow air, the HFNC may stabilize nasal airflow, facilitate nasopharyngeal dead-space washout, and improve breathing–swallowing coordination, thereby reducing respiratory effort and stress. These mechanisms contribute to the biological rationale for investigation, rather than being evidence of clinical effectiveness.

Additionally, the HFNC may improve the coordination between breathing and swallowing [3,4,5,6,7,12], a function that is critically challenged during dental procedures. A recent scoping review highlighted the conflicting results of studies that have explored the effects of the HFNC on swallowing function and swallowing–breathing coordination, confirming the need for context-specific feasibility studies before definitive effectiveness trials are undertaken [6]. These considerations further support the rationale for evaluating the HFNC under dental-specific conditions, rather than extrapolating findings from perioperative or critical care settings [1]. The primary objective of this pilot study is not to establish the clinical effectiveness of the HFNC in reducing stress but to determine whether its use during dental treatment might be feasible, acceptable to patients, and compatible with routine dental workflows. The assessed feasibility outcomes, including patient tolerance, acceptability, data completeness, and device-related safety, are essential prerequisites for the successful design and execution of future definitive clinical trials. Importantly, this study intends to demonstrate that HFNCs can be used in dental clinics and that comprehensive physiological and patient-reported data can be collected without disrupting standard dental procedures.

A distinctive strength of this study is its multidimensional assessment of stress-related outcomes by incorporating physiological parameters, autonomic nervous system indices, electroencephalographic activity, and patient-reported measures. Although these outcomes are explicitly exploratory, their inclusion offers valuable preliminary information on the feasibility and relevance of different outcome domains in dental settings. This approach is supported by recent systematic reviews on dental anxiety that emphasized substantial heterogeneity in outcome measures and highlighted the need for pragmatic, patient-centered endpoints that can be collected in routine clinical settings [10]. Concerns related to choking, gagging, or difficulty in managing saliva during treatment further reinforces the clinical relevance of interventions that can stabilize breathing and support breathing–swallowing coordination. Swallowing safety should be considered when applying HFNC to new clinical contexts, given that aspiration events have been reported during instrumented swallowing evaluations in certain clinical populations employing HFNCs [13].

Dental anxiety and treatment-related distress remain common clinical problems. Contemporary evidence highlights persistent gaps and heterogeneity in interventions aimed at reducing acute anxiety during dental procedures, underscoring the need for pragmatic, low-burden approaches that are easily integrated into routine workflow [1,14,15,16]. Such conditions may also amplify patient anxiety related to concerns about choking or an inability to swallow saliva effectively, which have been identified as important components of dental fear in both adult and pediatric populations [15,16].

### Limitations

This study has several limitations. First, it is a single-center, open-label, pilot feasibility study, and the findings are not intended to be generalizable or establish clinical efficacy. The exploratory analyses are not powered for hypothesis testing. Therefore, the results should be interpreted cautiously. However, these characteristics are inherent in pilot feasibility studies and are appropriate, given the primary objective of informing future study designs.

Second, the target sample size was determined pragmatically based on the annual number of eligible patients at the study institution and the anticipated consent rates, rather than on formal power calculations. Nevertheless, the comprehensive collection of physiological (EEG and ECG) and patient-reported data provides valuable preliminary information to guide the outcome selection and sample size estimation for subsequent confirmatory studies.

Third, the open-label, pre–post, fixed-sequence, within-subject feasibility design may be susceptible to expectation and sequence effects despite the inclusion of a washout period. In addition, stress and comfort will partly be assessed using self-reported questionnaires, which may be influenced by prior experience or recall bias.

Fourth, this study will use a fixed-sequence, within-subject comparison with the first full-mouth periodontal treatment without a HFNC, followed by a second session with a HFNC to minimize patient anxiety regarding HFNC use. Informed consent will be obtained before the interventions. However, a randomized crossover study design would be more appropriate for the objective evaluation of outcomes, as such a design could minimize the influence of period effects, learning or conditioning effects, and expectation bias, particularly when subjective endpoints such as comfort and anxiety are assessed. In the future, randomized crossover designs should be further examined.

Finally, the study will involve only patients undergoing full-mouth periodontal treatment (each session will be 30 min or less, with the patient in the supine position and no rubber dam). Future studies investigating the use of a HFNC during other dental procedures, such as extractions or endodontic therapy, are warranted. Furthermore, caution will be required when extrapolating these findings to other dental treatment contexts.

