### 2.6. Outcomes (Table 1)

#### 2.6.1. Primary Feasibility Outcomes

The primary feasibility outcomes are as follows:Recruitment ≥ 5/month (30 cases/6 months);Retention rates ≥ 70%;Patient tolerance and acceptability of the HFNC during dental treatment ≥ 80%;Completeness of physiological and questionnaire-based data collection ≥ 80%;Occurrence of device-related adverse events at less than 5% (less than one case).

**Table 1 dentistry-14-00208-t001:** Outcomes table.

Category	Outcome	Purpose
Primary (Feasibility)	Recruitment, retention	Trial feasibility
	Acceptability, tolerance	Practical implementation
	Data completeness	Outcome feasibility
	Adverse events	Safety
Secondary (Exploratory)	Pulse rate, respiratory rate	Stress physiology
	HRV (LF/HF)	Autonomic response
	EEG alpha activity	Neurophysiological stress
	Questionnaire	Patient-centered outcomes

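### The target of 30 equals the whole annual eligible pool, so the stated patient flow does not deliver it in any accrual period the article states once refusals are allowed for

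*Protocol article*

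**What the plan says.** Section 2.6.4 explains that "a formal sample size calculation based on statistical power was not performed". It gives one input, "Approximately 30 patients per year who meet the eligibility criteria are treated at the Department of Special Care Dentistry of Nagasaki University Hospital", and concludes from it that "a target sample size of 30 participants was considered feasible within the planned study period". Consent is not mentioned there, and the length of the study period is not given. The same sentence calls 30 sufficient for assessing recruitment, acceptability, data completeness and safety.

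The Limitations describe the same number differently: "the target sample size was determined pragmatically based on the annual number of eligible patients at the study institution and the anticipated consent rates". No consent rate appears as a number anywhere in the article.

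Section 2.6.1 gives the only accrual period in the article, as a primary feasibility criterion: "Recruitment ≥ 5/month (30 cases/6 months". The same list sets minimum marks of 70% for retention and 80% for tolerance and acceptability.

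**The concern.** The article gives two accounts of where 30 comes from. In section 2.6.4 the annual eligible number goes in and the same number comes out. In the Limitations, anticipated consent is a second input. Over one year, a consent rate below 100% would have to bring the target below the size of the pool, and it does not.

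Recruitment is itself a primary outcome, and the study is meant to inform the recruitment plan and sample size of a definitive trial. If the target and its period do not fit the stated patient flow, the recruitment criterion will fail for a reason already visible in the plan, and the failure will say little about patients' willingness to take part. The size also underlies the sufficiency claim. Tolerance of the HFNC and device-related events can be observed only in participants who reach session 2, since session 1 is done without the device.

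**Working it through.** **Inputs**

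- Eligible patients: about 30 per year (section 2.6.4), which is 30/12 = 2.5 per month.
- Target: 30 participants (section 2.6.4).
- Only stated accrual period: 6 months, at 5 or more per month (section 2.6.1).
- Retention: at least 70%, a minimum mark (section 2.6.1).
- Consent rate: not stated. The values from 50% to 90% below are assumptions, shown as a range.

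**Formula**

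Enrolled = eligible per year × (months/12) × consent rate.

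**Reproducing the plan's figure**

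30 × (12/12) × 1.00 = 30. The target is reproduced over one year only with full consent.

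**Over the stated 6 months**

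Eligible patients arriving: 30 × 6/12 = 15. Reaching 30 would need 30/15 = 200% consent. Equivalently, the mark of 5 per month is twice the eligible flow of 2.5 per month.

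**With refusals allowed for**

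| Assumed consent | Enrolled in 12 months (30 × consent) | Months to reach 30 (12 / consent) |
|---|---|---|
| 100% | 30 | 12.0 |
| 90% | 27 | 13.3 |
| 80% | 24 | 15.0 |
| 70% | 21 | 17.1 |
| 67% | 20 | 18.0 |
| 60% | 18 | 20.0 |
| 50% | 15 | 24.0 |

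The word approximately gives little slack. A shortfall of two patients corresponds to consent of 28/30, about 93%.

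**Number behind the tolerance and safety outcomes**

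If 30 are enrolled and retention is exactly at its minimum mark, 30 × 0.70 = 21 reach the HFNC session. Exact (Clopper-Pearson) 95% intervals for a result near the 80% tolerance mark:

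- 24 of 30: 61% to 92%, a width of about 31 percentage points.
- 17 of 21: 58% to 95%, a width of about 36 percentage points.

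This second step reflects attrition alone and involves no assumption about consent.

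**The case against.** The strongest reply is that no section fixes accrual at 12 months. Section 2.6.4 speaks of a planned study period without giving its length, and a longer period reconciles the two accounts exactly: 67% consent over 18 months, or 50% over 24 months, gives 30. A condensed article may leave study dates and the assumed consent rate to the full protocol. This stands in part. A reader might infer that no consent rate below 100% was applied, or that a year of recruitment will end well short of 30. The documents support neither statement. If enrolment continues until 30 is reached, refusals lengthen accrual and do not shrink the sample. The reply does not clear the plan, however, because the one period the article does print is 6 months, and that makes the mismatch larger.

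It can also be said that 70% is a minimum retention mark and not a forecast. That is right, so 21 is the number at the lowest acceptable retention and not an expected value. It would also be wrong to compare 24 of 30 with samples reduced by both assumed refusal and attrition and to attribute the whole loss of precision to consent.

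Finally, the study tests no hypothesis and discloses that its size is pragmatic. That limits the consequence. It does not make the size, the period and the patient flow agree.

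**Conclusion.** The concern holds in a limited form. The target of 30 equals the annual eligible pool, so within a year it leaves no room for refusal, although the Limitations say consent was considered. In the 6 months given in section 2.6.1, about 15 eligible patients arrive and 30 cannot be enrolled at any consent rate. The sections fit together only with accrual longer than a year, which the article does not state: 15 months at 80% consent, 18 at 67%, 24 at 50%.

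The 6-month result rests only on the article's own figures and on eligible patients arriving evenly. The longer accrual times rest on assumed consent rates. The effect on precision is modest: at minimum retention the exact interval near the tolerance mark is 58% to 95% with 21 exposed, against 61% to 92% with 30. The point should be corrected, but it does not stop the study from being run.

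**What to change.** Reconcile sections 2.6.1 and 2.6.4 and the Limitations:

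1. In 2.6.4, give the anticipated consent rate and the accrual period. Then restate either the time needed for 30 (12 / consent rate, in months) or the target achievable in the planned period (eligible per year × years × consent rate).
2. Set the recruitment mark in 2.6.1 to a monthly rate and a period that follow from that calculation.
3. Make the Limitations sentence match. Stating the consent rate or deleting the phrase about it is not enough alone, because the target and the period would still not fit the patient flow.
4. Base the sufficiency claim for tolerance and device-related events on the number expected to reach the HFNC session, with 21 of 30 as the figure at minimum retention, and give the resulting interval.

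The cost is a rewording of three places, and either a longer stated duration or a smaller stated size. No extra patients or procedures are needed.

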## 4. Conclusions

This RCT study is designed to assess the feasibility, acceptability, safety, and preliminary physiological effects of HFNC during periodontal treatment. By focusing on feasibility-related outcomes and exploratory patient-centered measures, this pilot study provides a methodological and physiological rationale for conducting a fully powered clinical trial to evaluate the effectiveness of the HFNC for improving breathing comfort and reducing treatment-related stress in routine dentistry in future-oriented studies.

These findings may suggest that delivering warmed and humidified high-flow air may address common sources of discomfort during dental treatment, particularly difficulties related to nasal breathing and swallowing saliva, which may contribute to dental anxiety. Although no conclusions regarding clinical effectiveness can be drawn from this exploratory pilot study, the results support subsequent confirmatory trials.

Ultimately, further research informed by these feasibility data has the potential to establish the HFNC as a novel, low-burden, patient-centered adjunct to routine dental care, with implications for improving treatment tolerance, safety, and overall oral health outcomes.

## Figures and Tables

**Figure 1 dentistry-14-00208-f001:**
[figure not shown]
Framework of the pre–post, fixed-sequence, within-subject feasibility design study.

**Figure 2 dentistry-14-00208-f002:**
[figure not shown]
Proposed physiological mechanisms by which a high-flow nasal cannula (HFNC) may influence breathing comfort during dental treatment. During routine dental procedures requiring sustained mouth opening, nasal airflow limitation, impaired breathing–swallowing coordination, and increased work of breathing may contribute to physiological stress responses. The HFNC delivers warmed and humidified high-flow air, which may stabilize nasal airflow, facilitate nasopharyngeal dead-space washout, and improve breathing–swallowing coordination under spontaneous breathing conditions. These mechanisms provide a biological rationale for investigating the HFNC as a patient-centered respiratory support strategy in the dental setting.

## Data Availability

The original contributions presented in this study are included in the article/Supplementary Materials. Further inquiries can be directed to the corresponding author.
